## **7. STATISTICS AND DATA ANALYSIS**

Logistic regression analysis will be used to identify predictors of development of acute kidney injury within seven days of admission. The scoring system (APS) developed from a previous Logistic regression analysis will be re-evaluated. The calibration of the scoring system will be assessed by the Hosmer-Lemeshow goodness-of-fit test. Discrimination will be assessed using the area under the receiver operating characteristic curve (AUC). Validation will be carried out by applying the scoring system comparing patients with AKI and those who did not develop AKI within 7 days.

Statistical analyses will be performed using SPSS v.19 with P-values below 0.05 considered as significant.

Data and all appropriate documentation will be stored for a minimum of 10 years after the completion of the study, including the follow-up period – as per MRC Good Research Practice Guidelines (2005).

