### **2.3 Trial statistics**

#### **Statistical methods**

#### **Sample size for original study**

Worthing Audit data Feb 2010-July 2010: 3400 patients admitted through the Acute Medical Unit:

n= 1746 with a pre-admission creatinine (51.3%)

Of this cohort n=184 had AKI on admission (11%) 1561 (88%) did not

Of remaining group n=1219 did not develop AKI

N=95 (7%) developed AKI during admission

Figure 1: Patient Flow Chart

[figure not shown]

Figure 1 – flow chart for initial derivation of Acute kidney injury physiological scoring (APS) system. Based on 6 months data and a cohort of 1746 patients who had a recent creatinine result.

|                              | Incidence | Hospital mortality |
|------------------------------|-----------|--------------------|
| AKI on admission to hospital | 11%       | 19%                |
| Hospital acquired AKI        | 7%        | 20%                |

The initial retrospective validation on the St Richard's site will involve a similar number of patients to enable statistical significance in terms of incidence of acute kidney injury to be assessed. A similar number of patients will then be assessed prospectively once the Acute kidney injury alert is introduced onto the Worthing site to allow comparisons between the two sites.

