### 3. STUDY DESIGN

2 parallel interrupted time-series design studies, on the Worthing & Chichester sites at WSHT, with segmented linear regression analysis in order to evaluate the longitudinal effect of intervention & controls for trends in outcome.

Initially (Phase 1) we will retrospectively review both sites to validate the score. Using the Chichester site this will add external validity to the APS score.

The alert will then be instituted (Phase 2) at the Worthing site during which time both sites will be monitored for the incidence of Acute kidney injury and adherence to the Patienttrack Assessment Pack at the Worthing site. After interim analysis, the plan will then be to roll-out the alert to the Chichester site and further analyses will then be performed.

Worthing and Chichester are relatively close geographically and demographics are similar making the use of the Chichester site as the initial 'control' arm methodologically sound. If there are significant differences in the two populations in terms of AKI incidence and outcomes, they will be picked up in the initial Phase 1 part of the study

Duration: 24 months

Cohort: All medical patients admitted as emergencies to WSHT two sites Acute Medical Units (AMU) and Becket ward and spend at least one night as an in-patient.

**Baseline data collection:** data will be retrieved from the Patienttrack, Pathology & PAS databases relevant to the 'AKI Patienttrack Assessment Pack'. This data will be transferred to an excel spreadsheet and then anonymised. This data will be stored on the WSHT server & only hospital password protected computers will be able to access this data. Anonymised data for mathematical & statistical analysis will be transferred by password protected & encrypted memory sticks or secure NHS e-mail.

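### Phase 1 assesses calibration only by a Hosmer-Lemeshow test, does not say that the score is applied unchanged, and is inconsistent about whether Worthing belongs to the validation

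*Protocol*

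**What the plan says.** Protocol section 7 holds the whole Phase 1 analysis in one paragraph. It starts with development: "Logistic regression analysis will be used to identify predictors of development of acute kidney injury within seven days of admission". It then turns to the existing score: "The scoring system (APS) developed from a previous Logistic regression analysis will be re-evaluated". For calibration it says: "The calibration of the scoring system will be assessed by the Hosmer-Lemeshow goodness-of-fit test". Discrimination is to be measured by the AUC. The last step is: "Validation will be carried out by applying the scoring system comparing patients with AKI and those who did not develop AKI within 7 days". The criterion throughout is: "Statistical analyses will be performed using SPSS v.19 with P-values below 0.05 considered as significant".

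On the site, section 3 says: "Initially (Phase 1) we will retrospectively review both sites to validate the score". The Phase 1 inclusion criteria in section 4.2 also name both Chichester and Worthing. The research question in section 1.1 and the design in section 2.2 put the external validation at Chichester. Section 1.2 says it is at another site, and section 2.3 places it at St Richard's (from context, Chichester). The caption to Figure 1 in section 2.3 labels the Worthing audit as the "flow chart for initial derivation of Acute kidney injury physiological scoring (APS) system".

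**The concern.** External validation asks whether the risks attached to a fixed score agree with what happens in new patients, and by how much they miss. A Hosmer-Lemeshow p-value does not answer that. A value above 0.05 may mean good agreement or too few events. A value below 0.05 does not say whether the score predicts too high, too low or too extremely. The same misfit is also more likely to be flagged as the cohort grows.

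The wording around the test adds two ambiguities. If the predictor search led to coefficients fitted in the validation data, the intercept and slope would be re-estimated before the test was run, and errors in them could no longer be seen. If Worthing results were pooled with Chichester's or reported under the same label, the reader could not tell performance at the derivation site from performance at a new one. What is at stake is the answer to the protocol's first aim.

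**Working it through.** **Inputs from the protocol (section 2.3).** The Worthing audit had 3,400 admissions, of whom 1,746 had a pre-admission creatinine. During admission 95 developed AKI and 1,219 did not. The evaluable group is 1,219 + 95 = 1,314, and the incidence is 95/1,314 = 7.2%, which agrees with the stated 7%. The validation is to use a similar number of patients, without a figure.

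**Assumptions.** The cohort is taken as N = 1,314 with predicted incidence 7.2%. The protocol gives no AUC or predictor strength. The main model has one normal predictor with a log-odds coefficient of 1 per SD. A second set of runs uses predictor strengths giving an AUC of about 0.71 or 0.79.

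**Test.** With ten risk groups, the statistic is the sum over groups of (O − E)² / [E(1 − E/n)], where O and E are observed and expected events. It is referred to chi-square with 10 df for frozen risks, or 8 df after refitting, at 0.05. The average group has 95/10 = 9.5 expected events.

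**Scenarios.** Over-prediction by 31%: predicted 7.2%, true 5.5% (7.2/5.5 = 1.31). Under-prediction by 31%: true incidence is 1.31 times the predicted one. Slope 0.7: overall incidence correct, but predictions too extreme.

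**Results, main model, N = 1,314 (chance of p < 0.05):**

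| Truth | Hosmer-Lemeshow, frozen risks | Hosmer-Lemeshow, refitted | Direct test |
|---|---|---|---|
| Calibrated | about 5% | about 5% | – |
| Over-prediction 31% | about 19% | about 5% | about 75% (intercept) |
| Under-prediction 31% | about 65% | – | – |
| Slope 0.7 | about 46% | about 5% | about 73% (slope) |

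Repeat runs differ by a few percentage points.

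**Sensitivity to predictor strength (frozen risks, AUC 0.71 / 0.79).** Observed/expected 0.8 is flagged 11% / 12%; 1.2, 35% / 35%; 1.5, 96% / 98%. Slope 0.8 is flagged 18% / 32%; slope 0.7, 34% / 62%; slope 0.5, 74% / 97%. After refitting, every scenario is flagged 3.5% to 5.8% of the time.

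**Sensitivity to N.** The 31% over-prediction is flagged about 31% of the time at N = 1,746 and about 75% at N = 3,400. A mild misfit (slope 0.9, observed/expected 1.1, AUC 0.71) is flagged 17% at 1,314, 30% at 3,400 and 69% at 10,000. The verdict on one and the same score therefore depends on how many records are extracted.

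**What an estimate would show.** With about 95 events the calibration slope has a standard error of about 0.147 (AUC 0.71) or 0.109 (AUC 0.79). The 95% interval is ±1.96 × 0.147 = ±0.29, or ±1.96 × 0.109 = ±0.21. That uncertainty is wide, and a p-value above 0.05 would hide it.

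**The case against.** Several points on the other side stand.

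- **Refitting.** A reader might infer that the APS will be refitted and the test therefore blind. Section 7 does not say so: it refers to a score from a previous regression and to validation by applying it. The 5% figures hold only under the refitting reading. What remains is that the text never says the score is unchanged.
- **Derivation site.** A reader might infer that the derivation patients are counted again as external validation. The sentence after the section 3 quote credits external validity to Chichester, and section 3 also uses Phase 1 to compare the two populations. No section calls Worthing external or shows that the February to July 2010 patients are re-used; later Worthing patients would give a temporal validation. What remains is the conflict with the sections that name only Chichester or another site.
- **Direction and size.** The test is weakest for over-prediction. It catches under-prediction far better, and finds observed/expected 1.5 on frozen risks 96% to 98% of the time. A larger cohort would also help.
- **Consequence.** A reader might infer that a lenient test lets the alert go live. No section makes deployment depend on a calibration result, and the alert shows categories, not probabilities, so ranking and cut-off performance matter more there. The AUC is planned.
- **SAP.** An interval for the AUC and accuracy at the cut-off may be in an SAP that is not shown; their absence is not part of this point. The choice of test and its 0.05 criterion are in the protocol itself.

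**Conclusion.** The concern holds as a should-fix. The protocol fixes one calibration method, and it suits the aim poorly. At about 95 events in 1,314 patients, 31% over-prediction would go unflagged about four times in five (1 − 0.19 = 0.81), a slope of 0.7 a little over half the time (1 − 0.46 = 0.54), and 31% under-prediction about one time in three (1 − 0.65 = 0.35). Direct tests of intercept and slope detect the first two about 75% and 73% of the time, and their estimates show size and direction.

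These figures rest on the assumed cohort size, predictor strength and degrees of miscalibration. The percentages move with those choices, but the lack of size and direction and the dependence on N do not go away. It is not a must-fix: refitting and re-use of derivation patients are not shown, gross under-prediction would be caught, and no decision rule hangs on the test.

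**What to change.** In section 7:

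1. State that the APS is applied unchanged, and that Chichester is the external validation.
2. Report calibration intercept, slope and a calibration plot with 95% confidence intervals, in place of or in addition to Hosmer-Lemeshow. Compare with the risks from the derivation model or, if those were not kept, with the observed derivation risk at each score level.
3. Make any search for predictors a later step, labelled as model updating.

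In sections 3 and 4.2, reconcile the site wording with sections 1.1, 1.2, 2.2 and 2.3. Report any Worthing result separately, as derivation-site or temporal validation according to which patients are used.

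The cost is some rewording, a little more analysis and the retrieval of the derivation risks. The protocol does not show whether those were kept. No new patient data are needed.

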### **Outcomes/ Analysis:**

Phase 1 – external validation of the APS to predict the development of Acute Kidney Injury on another hospital site

Phase 2 – can the introduction of an alert impact on:

- Incidence of AKI
- Magnitude of acute deterioration in Creatinine and estimated glomerular filtration rate (eGFR)
- Mortality
- Morbidity – secondary complications including other organ failures
- LOS
- Requirement for renal replacement therapies
- Requirement for escalation to critical care

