## **2. STUDY OBJECTIVES**

### **2.1 Trial objectives**

1. Retrospectively externally validate the APS
2. Can the use of an electronic prediction & identification alerting tool to deliver an individualised care bundle for hospital in-patients at risk of or with confirmed AKI reduce:
  - a. The incidence of AKI in those patients 'at risk'
  - b. The harm (mortality, morbidity, LOS) associated with failure to recognise those patients with confirmed AKI

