### 3.1 STUDY OUTCOME MEASURES

Outcomes data to be collected & analysed during the interrupted time-series design:

- Incidence of AKI
- Magnitude of acute deterioration in Creatinine, eGFR
- Compliance with AKI checklist
- Mortality
- Morbidity – secondary complications including other organ failures
- LOS
- Requirement for renal replacement therapies
- Requirement for escalation to critical care

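### No primary outcome is named for Phase 2, and the only significance rule is an unrestricted P<0.05 over seven unranked outcomes

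*Protocol*

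**What the plan says.** Section 1.1, under Outcomes/Analysis, introduces the effect question as "Phase 2 – can the introduction of an alert impact on" and lists seven items without ranking: AKI incidence, deterioration in creatinine and eGFR, mortality, morbidity, length of stay, renal replacement therapy, and escalation to critical care.

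Section 3.1 lists the same seven under "Outcomes data to be collected & analysed during the interrupted time-series design" and adds "Compliance with AKI checklist". The Study Summary has the same eight. No list marks an item as primary or secondary.

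Section 2.1 gives objective 2 two parts of equal standing. Part 2a is AKI incidence in at-risk patients. Part 2b is "The harm (mortality, morbidity, LOS) associated with failure to recognise those patients with confirmed AKI".

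Section 7 contains the only significance rule: "with P-values below 0.05 considered as significant". It has no restriction, ordering or adjustment. The methods described around it concern the validation of the prediction score.

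**The concern.** Naming the outcome that answers the research question is protocol content. Without it, a reader cannot tell which result would show that the alert works, and the choice can be made after the data are seen. The one stated threshold has a 5% error rate for a single test, not for the question of whether any of seven outcomes moved.

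The gap has a practical consequence. Section 3 plans to extend the alert to Chichester after an interim analysis, and does not say which outcome that analysis would judge. The sample-size text in Section 2.3 does not settle it either. It ties AKI incidence to the size of the retrospective validation, and sizes the prospective part only as a similar number of patients.

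**Working it through.** The Protocol states no family-wise error rate, so there is no figure of its own to reproduce. The check asks how often at least one test falls below 0.05 when the alert does nothing.

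**Inputs**
- Threshold per test: 0.05 (Section 7). Sidedness is not stated; two-sided is assumed.
- Number of tests: k = 7, one per item in Section 1.1. The longer list in Section 3.1 gives k = 8, shown for comparison.
- Correlation between test statistics: not given. Assumed equal for all pairs, range 0 to 0.9.

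**Why seven.** Checklist compliance measures use of the tool. Section 3 plans to monitor "adherence to the Patienttrack Assessment Pack at the Worthing site", during the period when the alert is in place, and gives no pre-alert or control value. It is not a test that an inert alert would pass or fail by chance, and Section 1.1 leaves it out of the effect question.

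**Independent tests**

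P(at least one) = 1 − (1 − 0.05)^k
- k = 7: 1 − 0.95^7 = 1 − 0.6983 = 30.2%
- k = 8: 1 − 0.95^8 = 1 − 0.6634 = 33.7%

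With no assumption about dependence, the Bonferroni bound is 7 × 0.05 = 35% for seven tests and 8 × 0.05 = 40% for eight.

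**Correlated tests.** Each statistic was simulated as z_i = √ρ·g + √(1−ρ)·e_i, with g and e_i independent standard normal, over 1,000,000 replicates. The figure is the share of replicates in which any |z_i| exceeded the two-sided 5% critical value.

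| ρ | 7 outcomes | 8 outcomes |
|---|---|---|
| 0.2 | 28.7% | 31.9% |
| 0.3 | 27.1% | 30.0% |
| 0.5 | 23.0% | 25.1% |
| 0.7 | 17.8% | 19.1% |
| 0.9 | 11.4% | 11.9% |

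**After the change.** One designated primary test at 0.05 has a 5% false-positive rate for the main claim. If all seven were instead kept on an equal footing with Bonferroni, each would be tested at 0.05/7 = 0.00714, and the family-wise error under independence would be 1 − (1 − 0.00714)^7 = 4.89%.

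**The case against.** **The threshold sentence is generic.** It closes a section otherwise about score validation, and no text says that each Phase 2 outcome will be declared separately or that one success is enough. This stands: a reader might infer such a rule, but the Protocol does not state it. The error rates here are therefore conditional on that use of the results. The sentence is still the only significance criterion given; if it does not govern Phase 2, Phase 2 has none.

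**Multiplicity can be left to a statistical analysis plan.** This stands for the adjustment method and the handling of secondary outcomes. It does not cover the missing primary outcome.

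**AKI incidence is already favoured.** It heads every list, is objective 2a, and is the outcome for which Section 3 says both sites will be monitored. That is emphasis, not designation, since objective 2b stands beside it. It does make the choice of primary outcome easy.

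**The outcomes overlap.** Creatinine change bears directly on AKI incidence, and organ failure, renal replacement, critical care, death and length of stay go together. This also stands, and is why the correlated figures matter more than the independent one.

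**Conclusion.** The point holds. Phase 2 has no primary outcome, and the stated threshold is not confined to any test. If any one significant result is read as evidence of benefit, the false-positive chance is up to about 30%, about 18% to 27% at correlations of 0.7 to 0.3, and about 11% at 0.9. Every case examined is more than twice the nominal 5%. The figures assume one test per listed outcome, two-sided normal statistics and equal correlation. They leave out the interim analyses, planned at least monthly (Sections 5 and 8.7).

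Two stronger readings are tempting and not supported:
- **One in three.** This needs eight outcomes, counting checklist compliance, and full independence. Neither suits an inert alert.
- **56% or 81%.** These come from 16 or 32 independent tests, counting a level and a slope change for eight outcomes at one or both sites. The Protocol specifies segmented regression but never says that both coefficients are separate claims. It also makes Chichester the initial control, so at that stage its coefficients are not extra chances to declare success.

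**What to change.** In Section 3.1, name one primary Phase 2 outcome. AKI incidence in at-risk patients is the natural choice because it is already objective 2a. State its time window. Objective 2a has none; the seven days that Section 7 uses for score validation is one option. Name one primary contrast, for example the change at Worthing relative to Chichester as control. The window and the contrast are suggestions for the sponsor to confirm.

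In Section 7, limit the P<0.05 claim to that test. Report the other outcomes as secondary, either with confidence intervals and no significance claim or with a Holm adjustment. For the six remaining effect outcomes, Holm's first step would be 0.05/6 = 0.0083.

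The cost is a few sentences. The downside is that a lone nominal P<0.05 on a secondary outcome, such as length of stay, can no longer be claimed as proof of benefit.

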## **8. REGULATORY ISSUES**

### **8.1 ETHICS APPROVAL**

Ethical approval will be sought and the trial will be conducted in compliance with the principles of the Declaration of Helsinki, the principles of GCP (for non-commercial trials, as defined by the Medical Research Council) and all of the applicable regulatory requirements.

### **8.2 CONSENT**

We will be placing posters in all wards where patient data will be analysed describing the purpose of the study and the care bundles (alert packs) being trialled. The alert being

instituted initially at Worthing recommends a bundle of best practice and as such is not a research intervention that could be consented for.

### **8.3 CONFIDENTIALITY**

Data retrieved from all these databases will be transferred to an excel spreadsheet and then anonymised. This data will be stored on the WSHT server & only hospital password protected computers will be able to access this data. Anonymised data for mathematical & statistical analysis will be transferred by password protected & encrypted memory sticks or secure nhs e-mail.

A report of the study findings will be submitted for publication in an appropriate scientific journal and/or international conference.

### **8.4 INDEMNITY**

NHS indemnity will apply. The Chief Investigator's organisation will be the organisation on which a claim is made. Compensation provision may be made through the 'Liabilities to Third Parties' scheme of the NHS Litigation Authority.

### **8.5 SPONSOR**

Sussex NHS Research Consortium

### **8.6 FUNDING**

It is envisaged that an application will be made to the NIHR for an RFPB grant to help with statistical, health economic analysis and ongoing running of the research.

### **8.7 AUDITS AND INSPECTIONS**

The Chief Investigator and the Study team will meet at least monthly to review the data and perform interim analysis of the results.

## **9. STUDY MANAGEMENT**

[name] Chief investigator and his study collaborators

## **11. PUBLICATION POLICY**

A report of the study findings will be submitted for publication in an appropriate scientific journal and/or international conference.

